**Figure 2 F2:**
[figure not shown]
Measured Ryodotens. Each Ryodoten represents the activity of respective meridian and the balance index will be calculated.

##### The change of HRV

2.6.1.2

The change of HRV will be analyzed by continuous heart rate recording with the HRM-Dual heart rate monitor (Garmin, Schaffhausen, Switzerland. https://buy.garmin.com/en-AU/AU/p/649059/pn/010-12883-00). It provides continuous heart rate record, transmits real-time heart rate data over ANT+ connectivity, and features a soft strap that is comfortable and adjustable. The heart rate will be recorded during the whole process for 2 and 1/2 hours so that the change in heart rate and HRV could be analyzed.

##### The change of checklist individual strength

2.6.1.3

The self-reported attention and fatigue questionnaire contains 30 items that are composed of subjective fatigue experience, concentration, motivation, and physical activity levels. Each item will be ranked from 1 to 5. Higher scores indicate higher distraction and fatigue levels. The questionnaires will be filled out 3 times: before intervention (baseline) and 1 and 2 hours after intervention.

##### The change of visual display terminals (VDTs) visual syndrome

2.6.1.4

The VDTs fatigue scale is a self-reported attention and fatigue questionnaire that focuses on visual syndrome and associated symptoms of long-time visual usage during work. VDTs fatigue scale has been applied and standardized by Japanese Ministry of Health, Labor, and Welfare survey results, 2004. VDTs fatigue scale is composed of 13 items. Each item ranks from 1 to 5. Higher scores indicate higher distraction and fatigue levels. The questionnaires will be filled out 3 times: before intervention (baseline) and 1 and 2 hours after intervention. This scale has been chosen as the method of evaluation for attention and visual fatigue due to the similar character of highly visual demand in archers and VDT workers.

#### Secondary outcome measures:

2.6.2

##### The change of motion stability

2.6.2.1

The change of motion will be recorded and analyzed by the WIMU PRO (RealTrack Systems, Almería, Spain. http://www.realtracksystems.com/wimu-pro/) throughout the whole process for 2 and 1/2 hours. WIMU is a tracking system with GPS/GNSS, 3D accelerometer, 3D gyroscope, 3D magnetometer, and WIFI 802.11 B/G/N, bluetooth 4.1, ANT+, and BLE.

### Statistical analysis

2.7

All data will be presented as mean ± standard deviation. Chi-square test or Fishers exact test will be applied to compare all patient characteristics and variables at baseline. Repeated measures analysis of variance will be used for comparison of the outcomes between ear and sham acupressures. Statistical significance will be considered at a *P*-value of <.05. All statistical analyses will be performed with SPSS software for Windows, version 25 (Statistics 25, SPSS, IBM Corp., Chicago, IL).

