### Study design

2.2

The study was started in October 2019 and planned to complete by December 2020. This is a crossover randomized controlled trial (Fig. 1). Each participant will be tested with 2 different interventions respectively. The participants will be randomized into ear-acupressure (EA) group (n = 17, anticipated) or sham-acupressure (SA) group (n = 17, anticipated), according to their order of appearance on the measuring day. Participants appearing in the odds order (1st, 3rd, 5th, etc) will be allocated to EA group whereas those appearing in the even order (2nd, 4th, 6th, etc) will be allocated to SA group. The trial participants and outcome assessors will be blinded after assignment to interventions using labels 1 and 2 for the 2 groups. The 2 interventions will be administered on the same day during 2 consecutive rounds of archery contest. The measurement will be performed at the archery ranges where participants used to practice archery.

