### Participants

2.3

Volunteered participants will be recruited from school teams among junior and senior high schools, and colleges in Kaohsiung, Taiwan through poster announcements in schools with archery club or school team and through internet. The investigator anticipates to enroll 34 participants, 17 each on EA and SA groups. Basic information including training duration of archery (1–3, 3–5, 6–10, and >10 years) and medical history will be collected. Inclusion criteria are healthy archers between 13 and 26 years old, who had been training for >1 year. Exclusion criteria include history of psychiatric disorders or cardiovascular diseases and previous surgical history of dominant hand. Those who are unwilling to provide informed consent will also be excluded. The study procedures and possible risks will be well explained to all the participants.

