### Sample size

2.4

26 participants were estimated to be needed based on repeated-measures analysis of variance with an effect size of 0.48, a significance level (α) of 0.05, and a desired power (1–β) of 0.80. The effect size was calculated from previous literature with G∗power, version 3.1.9.7 (Faul et al, 2020).^[12]^ In the study conducted by Molassiotis et al,^[13]^ the mean (standard deviation) of general fatigue scores at the baseline before the treatment were 16.6 (2.7) at the acupressure group, and 17.8 (2.5) at the sham acupressure group, and the mean (standard deviation) of general fatigue scores after completing the treatment were 14 (2.4) at the acupressure group, and 16.9 (3.0) at the sham acupressure group. Taking the potential 20% drop-outs into account, a total of 34 participants will be recruited.

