### Intervention

2.5

Ear acupressure: Vaccaria seeds are the mature seeds of *Vaccaria segetalis (Neck.) Garcke*, also known as cowherb, and wang-bu-lui-xing in Chinese. It is usually spherical in shape and about 1.5 to 2 mm in size. Vaccaria seeds will be attached by 3 M tape over auricular heart, liver, shen-men, and kidney points, under the application of the Chinese medicine physician who has >7 years of clinical service. Five minutes after administration, participants will start shooting a round of play with 36 arrows (within 40 minutes, including removal of arrows).

Sham acupressure: Same size of 3 M tape as in ear acupressure with a marked black point that looks similar to Vaccaria seed, will be attached over auricular heart, liver, shen-men, and kidney points. Five minutes after administration, participants will start shooting a round of play with 36 arrows (within 40 minutes, including removal of arrows).

Immediately after first round of play, the self-reported questionnaire will be filled out by the participants (V2). After sitting quietly for 15 minutes, the participants will receive Ryodoraku measurement. The Vacciria seeds/sham 3 M tape will be removed and switched to the other intervention (crossover) after the assessments are completed. Archers should rest for 15 minutes (including the time of obtaining written questionnaire and Ryodoraku measurement) between 2 rounds of play according to World Archery Federation rules. Next, the participants will start shooting the second round of play. Immediately after second round of play, the self-reported questionnaire will be filled out by the participants (V3). After sitting quietly for 15 minutes, the Ryodoraku measurement will be performed. Participants could cease the experiment if unbearable discomfort is experienced or unstable vital condition is observed during intervention, or under any personal request to stop the process.

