##### The change of meridian activities

2.6.1.1

The meridian activities and balance index will be measured and calculated with Ryodoraku device (Meridian Energy Analysis Device, MEAD, medpex, Taiwan). It will be measured 3 times: before intervention (baseline) and 1 and 2 hours after intervention. The meridian activities will be shown by numbers calculated by the skin electric resistance. The higher the number, the higher is the meridian activity, and vice versa. Before the Ryodoraku measurement, the participants need to take off their shoes and socks, remove all metal accessories, cellphone, medication, electronic devices on their body, clean their hands and feet, and lie down on the plastic bed. During the measurement, the participant must not contact any metal obstacle and the investigator will not touch the participant. The 12 measured Ryodotens will be as follows (Fig. 2): Taiyuan (LU9) on the Lung meridian, Daling (PC7) on the Pericardium meridian, Shenmen (HT7) on the Heart meridian, Yanggu (SI5) on the Small Intestine meridian, Yangchi (TE4) on the Tripple Energizer meridian, Yangxi (LI5) on the Large Intestine meridian, Taibai (SP3) on the Spleen meridian, Taichong (LR3) on the Liver meridian, Dazhong (KI4) on the Kidney meridian, Shugu (BL65) on the Bladder meridian, Qiuxu (GB40) on the Gallbladder meridian, and Chongyang (ST42) on the Stomach meridian. Each first detected data will be viewed as the activity of that Ryodoten.

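### The stated repeated-measures ANOVA does not fit the two-period crossover: it names no intervention-received, period or sequence term and no tested contrast

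*Protocol article*

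**What the plan says.** Section 2.2 (Study design) sets up a crossover: "Each participant will be tested with 2 different interventions respectively", and "The 2 interventions will be administered on the same day during 2 consecutive rounds of archery contest". The EA and SA groups of 17 each are defined there by the intervention received first, so they are the two sequences, EA then SA and SA then EA. Section 2.3 repeats the split: "The investigator anticipates to enroll 34 participants, 17 each on EA and SA groups".

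Section 2.5 (Intervention) places the switch between the second and third assessments: the seeds or sham tape "will be removed and switched to the other intervention (crossover) after the assessments are completed". The third assessment therefore follows the other intervention.

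Section 2.6.1.1 gives the times for the Ryodoraku outcome: "It will be measured 3 times: before intervention (baseline) and 1 and 2 hours after intervention". Sections 2.6.1.3 and 2.6.1.4 give the same times for the two questionnaires.

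Section 2.7 (Statistical analysis) has one sentence on the treatment comparison: "Repeated measures analysis of variance will be used for comparison of the outcomes between ear and sham acupressures". Section 2.4 sizes the trial on the same method: "26 participants were estimated to be needed based on repeated-measures analysis of variance with an effect size of 0.48", with "a significance level (α) of 0.05, and a desired power (1–β) of 0.80".

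**The concern.** In a two-period crossover the treatment effect is a within-person contrast between rounds, separated from any difference between the rounds themselves. Section 2.7 does not say whether the factor is the first-assigned group or the intervention received in each round, does not mention period or sequence, and does not say which effect is tested. The time labels in Section 2.6 read as if one intervention were followed for two hours, which invites a parallel-group analysis of EA and SA groups over three times.

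A period effect is plausible. The second round follows 36 arrows already shot, and fatigue is itself among the primary outcomes. The readings of Section 2.7 differ in what they estimate and in their power, and the text leaves the choice open until after the data are seen.

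**Working it through.** **The plan's own figure.** Inputs from Section 2.4: effect size 0.48 (taken as Cohen's f, an assumption), alpha 0.05, power 0.80. The within-person correlation rho is not given, so 0.5 is assumed. There are two groups and m measurements.

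- Between-groups test: lambda = f² × N × m / (1 + (m - 1) × rho), with 1 and N - 2 df. With m = 3 and N = 26, lambda = 0.2304 × 26 × 3 / 2 = 8.99 and power is 0.820. At N = 24 power is 0.786, so 26 is the first even N that reaches 80%.
- With m = 2 and rho = 0.5 the same test needs 28. With m = 2 and rho of 0.3 or 0.4 it again gives 26.
- Within-subject or interaction test: lambda = f² × N × m / (1 - rho). This needs only 10 (m = 3) or 12 (m = 2).
- Drop-out: 26 / 0.8 = 32.5, rounded up to 33, or 34 for equal groups, as stated.

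The stated 26 is therefore matched by a between-groups test and not, at rho = 0.5, by a within-person one. This is an inference, because the correlation and the G*Power test are not stated.

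**Cell means.** Let T be the treatment effect and P the shift from round 1 to round 2, with no carry-over.

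| First intervention | Baseline | After round 1 | After round 2 |
|---|---|---|---|
| EA | 0 | T | P |
| SA | 0 | 0 | P + T |
| Difference | 0 | +T | -T |

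**Reading A: EA/SA group by three times.**

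- Group main effect: (T + P)/3 - (P + T)/3 = 0 for any T and P. In simulation with 13 per sequence, SD 1, rho 0.5 and T = 1 SD, it rejects 4.7% of the time, which is the nominal level.
- Group-by-time interaction: the differences 0, +T, -T do not cancel. With n = 13 per sequence and error variance 1 - rho = 0.5, lambda = (13/2) × 2T² / 0.5 = 26T², on 2 and 48 df.
- Crossover contrast, ((round 1 - round 2 in EA-first) - (round 1 - round 2 in SA-first))/2: it equals T for any P. The within-person difference has variance 2(1 - rho) = 1, so lambda is again 26T², but on 1 and 24 df.
- At T = 0.57 SD, lambda = 26 × 0.3249 = 8.45. Power is 71% for the interaction and 80% for the contrast. At T = 1 SD it is 99.6% and 99.8%.

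The interaction has the same non-centrality but spends two numerator degrees of freedom, and it yields no EA-SA estimate.

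**Reading B: intervention received, without period.** The EA minus SA difference has mean T - P in EA-first participants and T + P in SA-first participants. With equal sequences the average is T, and P goes into the error term. With n1 and n2 completers the bias is -P(n1 - n2)/(n1 + n2).

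| Setting | Result without period |
|---|---|
| 13/13, T = 0.57, P = 0 | power 80% |
| 13/13, T = 0.57, P = 0.5 | power 72% |
| 13/13, T = 0.57, P = 1 | power 49% |
| 13/13, T = 0, P = 0.5 or 1 | type I error about 0.03 or 0.005 |
| 14/12, P = 0.5 | bias -0.5 × 2/26 = -0.04 SD |
| 16/10, P = 1 | bias -1 × 6/26 = -0.23 SD |

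With period in the model, power stays at about 80% for every P.

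**The case against.** The strongest reply is that Section 2.7 compares ear with sham acupressure, that is, interventions and not allocated groups, and that Section 2.2 says each person receives both. A within-person comparison is at least as natural a reading. Under it, with balanced sequences, leaving out period biases nothing and makes the test conservative. That stands, and so does the reply that the values of T and P and the completion splits above are assumptions. A 16/10 split means losing 1 of 17 in one sequence and 7 of 17 in the other within a single session of about two and a half hours.

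It also stands that group is sequence and time contains period under the group-by-time reading. A reader might infer that the treatment effect as a whole cancels, or that a real effect could not be detected. The documents do not support this: only the group main effect is zero, and the interaction keeps the signal. Nor does cancellation automatically reach heart rate variability or motion stability, which are recorded continuously.

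A reader might also see a conflict between an ANOVA that drops incomplete cases and Section 2.8. That section promises only to collect data from those who discontinue, not to include them in this analysis, so there is no contradiction.

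Finally, an article may leave model terms to a fuller plan. Here, however, it states a method, and the method as stated does not match the design. With complete data, a group-by-round interaction on the two post-intervention values would be the same test as the contrast recommended here, but the text does not specify it.

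**Conclusion.** The concern holds as a mismatch between the stated analysis and the crossover design. One effect that the sentence permits, the EA/SA group main effect over three times, estimates zero treatment effect. It is also the kind of test that best matches the stated sample size, given an assumed correlation.

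The other routes remain sensitive to treatment but are inferior. The interaction loses about 9 percentage points of power at T = 0.57 SD and gives no direct estimate. The paired comparison without period loses about 8 or 31 points at assumed period shifts of 0.5 or 1 SD, and is biased if the sequences complete unequally.

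All the power figures rest on 13 per sequence, SD 1, correlation 0.5 and alpha 0.05. The exact zero also requires complete data and no carry-over.

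**What to change.** Replace the treatment sentence in Section 2.7 with: *For each outcome, the round-1 and round-2 values are analysed by a linear mixed model with fixed effects for intervention received (EA or SA), period (round 1 or 2) and sequence, and a random participant effect. The EA-SA contrast with its 95% confidence interval is the treatment effect. All available rounds are used.*

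In Sections 2.6.1.1, 2.6.1.3 and 2.6.1.4, relabel the two later time points as end of round 1 and end of round 2.

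The cost is one rewritten sentence, three relabelled passages and a few lines of syntax. The mixed-model procedure in the SPSS version already named fits this model, and no new data are needed.

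### Four unranked primary outcomes share one unadjusted 5% threshold, so the chance of a false-positive primary finding is about 13–19% with one test per outcome, and more if the meridian readings are tested singly

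*Protocol article*

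**What the plan says.** Section 2.6.1 of the protocol article places four outcomes under the primary heading, with nothing to mark one as the main one:

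- Section 2.6.1.1: "The meridian activities and balance index will be measured and calculated with Ryodoraku device". The site list opens with "The 12 measured Ryodotens will be as follows", and the section ends "Each first detected data will be viewed as the activity of that Ryodoten". This one primary outcome therefore produces 12 values and an index at each measurement.
- Section 2.6.1.2: "The change of HRV will be analyzed by continuous heart rate recording". No particular HRV index is named, and change in heart rate is mentioned as well.
- Section 2.6.1.3, on the checklist individual strength: "The self-reported attention and fatigue questionnaire contains 30 items".
- Section 2.6.1.4, on the visual scale: "VDTs fatigue scale is composed of 13 items".

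Section 2.7 covers all of them with one method, "Repeated measures analysis of variance will be used for comparison of the outcomes between ear and sham acupressures", and one criterion, "Statistical significance will be considered at a *P*-value of <.05".

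Section 2.4 sizes the trial at 26 participants, or 34 after allowing for 20% drop-out. The inputs are an effect size of 0.48, alpha 0.05 and power 0.80, and the effect size comes from general fatigue scores in an earlier acupressure trial.

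**The concern.** A 5% threshold protects a trial's main claim at 5% only if there is one test behind that claim, or if every one of several tests must succeed. Here there are at least four tests, and the article says neither that one is decisive nor that all must be positive. Under the rule as written, a significant result on any of the four could be reported as a positive primary finding.

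The Discussion hypothesises effects on autonomic function and meridian activity and, through them, on performance. It also reports that sham-controlled trials of acupuncture on HRV gave variable results. In that setting an isolated chance finding, perhaps on one skin-resistance reading or on an HRV index chosen later, could pass for confirmation.

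**Working it through.** **1. The plan's own sample size.** Inputs from section 2.4: f = 0.48, alpha = 0.05, power = 0.80. Assumed here, because the article does not state them: the between-groups form of repeated-measures ANOVA, m = 3 measurements, correlation r = 0.5.

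- Noncentrality: λ = f²·N·m / [1 + (m − 1)r].
- At N = 26: λ = 0.2304 × 26 × 3 / 2 = 8.99. With F on 1 and 24 degrees of freedom, power is 0.82.
- At N = 24: power is 0.79. So 26 is the smallest even total that reaches 80%.
- Drop-out: 26 / 0.8 = 32.5, so 33, or 34 for equal groups.

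The stated 26 and 34 are reproduced with the whole 0.05 spent on one test.

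**2. Number of tests.** The least the article allows is one per primary outcome, which is 4. If the meridian readings are analysed singly, the count is 12 readings + 1 balance index + 1 HRV index + 2 questionnaire totals = 16.

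**3. Chance of at least one false positive, independent tests, no true effect.** Formula: 1 − 0.95^k.

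- k = 4: 1 − 0.8145 = 18.5%
- k = 13 (meridian variables alone): 1 − 0.5133 = 48.7%
- k = 16: 1 − 0.4401 = 56.0%

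**4. The same with positive correlation.** The article gives no correlations, so a range was simulated using equicorrelated two-sided z tests, each at 0.05.

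| Correlation | 4 tests | 16 tests, all correlated | 13 correlated + 3 independent |
|---|---|---|---|
| 0 | 18.5% | 56% | 56% |
| 0.3 | 17.4% | 47% | 50% |
| 0.5 | 15.6% | 37% | 43% |
| 0.7 | 13.0% | 26% | 35% |

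**5. Power cost of keeping four primaries.** Bonferroni, and the first step of Holm, test at 0.05 / 4 = 0.0125. Two models were used:

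- the ANOVA model of step 1;
- a crossover t test with n − 2 degrees of freedom, at the within-person difference detectable with 80% power at n = 26 and alpha 0.05, which is 0.573 SD.

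| Evaluable participants | Alpha | ANOVA model | Crossover t test |
|---|---|---|---|
| 26 | 0.05 | 82% | 80% |
| 26 | 0.0125 | 62% | 59% |
| 34 | 0.0125 | 78% | 75% |

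In the ANOVA model, 80% power at 0.0125 needs 36 evaluable participants, more than the 34 to be recruited. In the crossover model the detectable difference at 26 rises from 0.573 to 0.701 SD. Since (0.701 / 0.573)² = 1.50, that corresponds to about 50% more participants.

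**The case against.** The strongest reply is that the article is being read too literally. Section 2.7 does not say that the 12 meridian readings are tested one by one. A summary, or one ANOVA with meridian as a within-person factor, would fit the text equally well. Nor does a threshold of .05 rule out adjusted P values, and an analysis plan that is not shown may contain an adjustment. The readings come from one device, in one session, on one person, so independence is implausible. And in a small study of immediate effects in healthy archers, reporting every domain with confidence intervals and cautious claims is defensible.

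Much of this stands, and it limits the size of the point. A reader might infer that a chance positive primary result is likely, meaning more probable than not. The article does not support that: a figure above 50% needs 16 separate tests that are close to independent, and the article states neither.

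The core remains. The article itself fixes four unranked primaries and one unqualified threshold, and its sample size makes no allowance for more than one test. An unseen plan would have to alter that position, not merely add detail to it. Even one test per outcome with correlation 0.7 gives 13%, more than twice the nominal 5%.

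**Conclusion.** The concern holds in a limited form. With four unranked primaries each judged at .05, the probability of at least one false-positive primary is about 13–19% with one test per outcome (correlation 0.7 down to 0). It rises to about 26–56% if the meridian readings and the other variables are tested as 16 separate comparisons.

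The figures rest on three assumptions: no true effect on any outcome, any single positive counting as success, and correlations between 0 and 0.7. The article does not settle the second or supply the third. The lower range is the safer one to quote, because it needs no assumption about how the 12 readings are analysed.

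**What to change.** Preferred: before unblinding, and by dated amendment, name one variable from the four listed primary outcomes, test it at 0.05 and make the rest secondary. The checklist (fatigue questionnaire) total is closest to the basis of the sample size, since section 2.4 uses a fatigue score. This costs no alpha. The shooting score may look like the natural choice, and the Abstract and Discussion mention it, but section 2.6 does not list it as an outcome and section 2.4 offers no effect size for it. Promoting it would be a change of primary outcome, not a clarification.

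Alternative: keep four primaries with one summary each (the balance index, one named HRV index and the two questionnaire totals) under Holm's procedure at a family-wise 0.05. Report the 12 individual meridians as exploratory with 95% confidence intervals. This is not a wording change only. Worst-case power per outcome, at the first Holm step, is about 59–62% with 26 completers and about 75–78% with 34, so the stated 80% must be restated or the sample size revisited.
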